## Abstract

**Background:**

Postcancer fatigue is a frequently occurring, severe, and invalidating problem, impairing quality of life. Although it is possible to effectively treat postcancer fatigue with cognitive behaviour therapy, the nature of the underlying (neuro)physiology of postcancer fatigue remains unclear. Physiological aspects of fatigue include peripheral fatigue, originating in muscle or the neuromuscular junction; central fatigue, originating in nerves, spinal cord, and brain; and physical deconditioning, resulting from a decreased cardiopulmonary function. Studies on physiological aspects of postcancer fatigue mainly concentrate on deconditioning. Peripheral and central fatigue and brain morphology and function have been studied for patients with fatigue in the context of chronic fatigue syndrome and neuromuscular diseases and show several characteristic differences with healthy controls.

**Methods/design:**

Fifty seven severely fatigued and 21 non-fatigued cancer survivors will be recruited from the Radboud University Nijmegen Medical Centre. Participants should have completed treatment of a malignant, solid tumour minimal one year earlier and should have no evidence of disease recurrence. Severely fatigued patients are randomly assigned to either the intervention condition (cognitive behaviour therapy) or the waiting list condition (start cognitive behaviour therapy after 6 months). All participants are assessed at baseline and the severely fatigued patients also after 6 months follow-up (at the end of cognitive behaviour therapy or waiting list). Primary outcome measures are fatigue severity, central and peripheral fatigue, brain morphology and function, and physical condition and activity.

**Discussion:**

This study will be the first randomized controlled trial that characterizes (neuro)physiological factors of fatigue in disease-free cancer survivors and evaluates to which extent these factors can be influenced by cognitive behaviour therapy. The results of this study are not only essential for a theoretical understanding of this invalidating condition, but also for providing an objective biological marker for fatigue that could support the diagnosis and follow-up of treatment.

**Trial registration:**

The study is registered at http://ClinicalTrials.gov (NCT01096641).

## Background

### Postcancer fatigue

Postcancer fatigue (PCF) is a frequently occurring, severe, and invalidating problem in cancer survivors, impairing quality of life.[1,2] About 70 to 96% of the cancer patients undergoing chemotherapy and/or radiotherapy experience symptoms of fatigue.[3,4] The prevalence of PCF observed in longitudinal follow-up studies ranged from 19 to 39%.[1,5-8] Previous disease and treatment characteristics are unrelated to PCF.[2,4,9-12] However, there is some evidence that patients who are treated with only a surgery are less at risk for PCF[8] and survivors who are treated with more aggressive treatments are more at risk for PCF [1,13]. Cognitive behaviour therapy (CBT), especially designed for PCF, seemed to be an effective treatment option for PCF.[11,14] However, although it is now possible to effectively treat PCF, the nature of the underlying physiology of PCF remains unclear.

The term fatigue in the medical literature usually refers to fatigue experienced by the patient, but it can also refer to physiological fatigue. Fatigue experienced by the patient and its psychological aspects can be quantified using questionnaires. Physiological aspects of fatigue include peripheral fatigue, originating in muscle or the neuromuscular junction; central fatigue, originating in nerves, spinal cord, and brain; and physical deconditioning, resulting from a decreased cardiopulmonary function.

### Peripheral and central fatigue

In physiology, fatigue is usually defined as the loss of voluntary force-producing capacity during exercise,[15] which can have a peripheral and a central origin.[16] During peripheral muscle fatigue, membrane excitability of muscle tissue is influenced due to a decrease in pH, accumulation of lactate, and changes in intra- and extracellular ion concentration.[17] Muscle fibre conduction velocity (MFCV), which can be determined by surface electromyography (sEMG), reflects the peripheral situation.[16] Alternatively, peripheral fatigue can be quantified by measuring the muscular force response to artificial electrical stimulation before and after exercise. Besides peripheral factors, a failure of drive from the central nervous system may also contribute to fatigue[18] This sub-maximal central activation during exercise, or central activation failure (CAF), is named central fatigue[16] and can be measured with a twitch interpolation technique.[19]

Physiological fatigue has been studied in patients with neuromuscular diseases,[20] in patients with chronic fatigue syndrome (CFS),[21] but also in cancer patients to evaluate cancer-related fatigue.[22] In a study of 16 cancer patients referred to palliative medicine and 16 matched non-cancer controls, neuromuscular testing was applied to determine whether cancer-related fatigue is a more centrally or peripherally mediated disorder.[22] Patients suffering from cancer-related fatigue showed less peripheral muscle fatigue and more central muscle fatigue compared to their non-fatigued controls.

It should be noted that some psychological aspects of fatigue are different for different neuromuscular diseases[23] as well as for fatigue in CFS and for cancer-related fatigue. Nevertheless, CAF appears to be a shared neurophysiological feature of fatigue in all these diseases. Therefore, it is of great interest to know whether PCF is also characterized by CAF.

Although CAF implies a central origin of fatigue, it is still unclear from which part of the central nervous system the failure originates. Therefore, further studies on brain morphology and brain metabolism are essential to elucidate the (neuro)physiological basis of fatigue.

### Brain morphology and metabolism

Using magnetic resonance imaging (MRI), several studies have reported structural abnormalities in the brains of patients with CFS. In a group of 259 fatigued patients, specific hyperintense small punctuated subcortical white-matter foci were observed.[24] Similar results have been reported by others.[25-27] Different research groups conducted voxel-based morphometry (VBM) in CFS patients and matched healthy controls and observed gray matter volume reductions in fatigued patients compared to non-fatigued controls.[28,29] Interestingly, it has been shown that CFS patients showed a significant increase in gray matter volume, localized in the lateral prefrontal cortex, after CBT.[30]

Magnetic resonance spectroscopy (MRS) provides a non-invasive window on metabolism in the brain. Studies with proton (^1^ H) MRS allow the detection and quantification of metabolites like choline, creatine, N-acetylaspartate, and lactate. Choline is a precursor of membrane phospholipids and an elevated choline level has been associated with increased cell membrane turnover, cell density, and gliosis. Choline levels vary over the brain and the choline to creatine ratio is higher in white matter than in gray matter. In a ^1^ H MRS study of the brain of CFS patients and eight age- and sex-matched healthy control subjects, the mean ratio of choline to creatine in the occipital cortex of fatigued patients was significantly higher compared to healthy controls.[31] The amount of creatine in the brain is assumed to be constant. An increased choline to creatine ratio suggests an abnormality of phospholipid metabolism and/or associated brain morphology. Similarly, in a ^1^ H MRS study of the left basal ganglia, a highly significant increase in the signal from choline-containing compounds was seen in CFS patients compared to age- and sex-matched healthy controls.[32] In three children with CFS, ^1^ H MRS demonstrated a significantly higher choline to creatine ratio in the frontal cortex compared to healthy controls.[33] N-acetylaspartate is considered to be a marker of neuronal density and neuronal function. In one study, reduced levels of N-acetylaspartate were observed in the right hippocampus of seven CFS patients compared to healthy controls.[34] Elevated lactate in the brain may suggest cerebral energy dysfunction. The presence of elevated ventricular lactate was observed in sixteen CFS patients as compared to healthy controls.[35]

Especially for CFS, certain characteristics of brain morphology and metabolism may serve as objective biomarkers for fatigue. However, since CFS and PCF differ in some psychological aspects[36] it still needs to be shown that these characteristics also play a role in PCF.

### Physical condition and activity

Despite the fact that current cancer treatments are increasingly efficacious for improving survival, they are toxic in numerous ways. Therefore, many cancer patients are forced to decrease their physical activity, possibly leading to physical deconditioning. Physical activity levels were significantly reduced after diagnosis in a study of 812 breast cancer patients.[37] It may be hypothesized that compared to non-fatigued cancer survivors, PCF patients have an impaired physical condition due to decreased physical activity after cancer treatment.

In a previous study comparing physical condition in a group of 20 CFS patients and 20 matched non-fatigued sedentary controls, physical condition did not significantly differ between both groups. Although as a clinical syndrome CFS and PCF show strong similarities, in PCF a clear precipitating moment can be identified that provoked fatigue, namely the diagnosis of cancer and its subsequent treatment. In contrast to PCF, not always a precipitating factor can be identified in CFS. Therefore, studies on physical condition, specifically in cancer survivors, are needed to investigate the physiology of PCF.

## Methods/design

### Study design

A randomized controlled trial (RCT) with 6 months follow-up will be conducted to identify and measure (neuro)physiological factors of fatigue in severely fatigued disease-free cancer survivors and to determine the role of these factors in the maintaining of fatigue. At baseline, fatigued and non-fatigued patients will undergo measurements for peripheral and central fatigue, brain morphology and metabolism, and physical condition and activity. Fatigued patients will be randomly assigned to either the intervention group, who will immediately start CBT, or the control group, who will start CBT after six months. After six months follow-up, the measurements will be repeated in both groups of fatigued patients.

### Ethical consideration

This study has been approved by the Medical Ethical Committee of the Radboud University Nijmegen Medical Centre (RUNMC). Patients will be informed about the study and informed consent will be obtained before randomization.

### Study population

Patients who have been curatively treated for cancer and finished treatment at least one year before, will be asked by their physician to fill out the Checklist Individual Strength (CIS),[38] RAND-36,[39] Beck Depression Inventory for Primary Care (BDI-pc),[40] and some additional demographic and medical questions during their control-visits. Based on the scores of the fatigue severity subscale of the CIS (CIS-fatigue), patients with a cut-off score of ≥35 will be classified as severely fatigued. Severely fatigued patients, who are referred to the Expert Centre for Chronic Fatigue of the RUNMC and who met the in- and exclusion criteria of the study (Table 1), will be informed by their treating psychologist about the study. If the patients agree to be further informed about the study, the researcher will inform the patients extensively about the study and will ask for participation. Severely fatigued patients will be matched with non-fatigued patients with respect to age, sex, and previous cancer treatment (Figure 1). A total number of 57 severely fatigued and 21 non-fatigued cancer survivors will be included (see power calculation).

**Table 1 T1:** Inclusion and exclusion criteria

**Inclusion criteria**	(1) Age between 19 and 65 years
	(2) Age at disease onset minimal 18 years
	(3) Treated for a malignant, solid tumour
	(4) Completion of treatment for cancer minimal 1 year ago (single treatment modality surgery/ current hormonal therapy permitted)
	(5) Disease-free, as defined by the absence of somatic disease activity parameters
**Exclusion criteria**	(1) Physical comorbidity that could explain the fatigue
	(2) Current psychological or psychiatric treatment
	(3) Brain tumour in the past
	(4) Contra-indication for MR examinations (e.g. claustrophobia)
	(5) Treatment with anti-depressive drugs, anti-epileptic drugs, or benzodiazepines
	(6) Insufficient command of the Dutch language to fill out questionnaires

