### Statistical analysis

Independent samples *t* tests will be performed testing baseline differences in primary and secondary outcome measures between fatigued and non-fatigued cancer survivors. Baseline differences between the therapy and waiting list condition are entered as covariates in further analyses. A paired *t* test will be performed to test whether differences can be observed within the therapy or waiting list condition from baseline to follow-up. Differences between the therapy and waiting list group on the change in outcome measures from baseline to 6 months later will be calculated with analyses of covariance (ANCOVA).

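### Exclusion criterion 1 is defined relative to fatigue, so read literally it can remove only fatigued survivors and may leave comorbidity in the non-fatigued controls

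*Protocol article*

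**What the plan says.** The first exclusion in Table 1 of the protocol article is "Physical comorbidity that could explain the fatigue".

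The only sentence under Study population that cites Table 1 is about the fatigued group. Its subject is "Severely fatigued patients, who are referred to the Expert Centre for Chronic Fatigue of the RUNMC", and it continues "who met the in- and exclusion criteria of the study (Table 1), will be informed by their treating psychologist about the study". For the comparison group the section says: "Severely fatigued patients will be matched with non-fatigued patients with respect to age, sex, and previous cancer treatment".

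Both groups have the full set of baseline assessments: "At baseline, fatigued and non-fatigued patients will undergo measurements for peripheral and central fatigue, brain morphology and metabolism, and physical condition and activity". Under Statistical analysis, independent samples "tests will be performed testing baseline differences in primary and secondary outcome measures between fatigued and non-fatigued cancer survivors". No adjustment is stated for that comparison. The covariates mentioned in the next sentence concern baseline differences between therapy and waiting list. The Power calculation section gives the matched baseline comparison the task of identifying the (neuro)physiological characteristics of fatigue.

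**The concern.** Exclusion 1 cannot be applied as worded to someone without fatigue. Take two survivors with the same heart or lung disease. The fatigued one is excluded because the disease might account for the fatigue. The non-fatigued one meets no such exclusion. If sites follow the words, the cases are cleared of such disease and the controls need not be.

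Several outcomes are ones that cardiopulmonary or neuromuscular disease can lower directly: VO2max, daily activity and muscle performance. Disease left only in the controls would pull their mean towards that of the fatigued group. The article hypothesises an impaired physical condition in the fatigued group and seeks an objective biological marker of fatigue, and this imbalance would work against finding either. Because the error comes from selection, a larger sample would not remove it.

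**Working it through.** **Can exclusion 1 reach a control?** There are two ways to read the scope of Table 1.

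- *Table 1 covers both groups.* The item still refers to a fatigue that a control does not have. Literally applied, it removes fatigued survivors only.
- *Table 1 covers the referred fatigued patients only.* The item does not reach controls at all.

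The wording problem is present either way, so it does not depend on settling the scope.

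**Does another stated step repair it?**

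- Matching: age, sex and previous cancer treatment. Comorbidity is not among them.
- Analysis: t tests between fatigued and non-fatigued survivors, with no covariates stated.

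Neither step addresses comorbidity.

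**The plan's own control number.** The article requires 20 non-fatigued patients and assumes 5% technically insufficient data: 20 / 0.95 = 21.05, in line with the stated 21. The point here does not change that figure.

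**Illustrative size.** Let q be the share of controls with a condition that would have excluded a fatigued patient, and e its effect on an outcome in SD units. Assume no such condition remains among the cases. The control mean falls by q × e, and a true deficit D appears as D − q × e. The article gives neither q nor e. The values below are assumptions.

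| q | e (SD) | q × e (SD) | a true 0.5 SD deficit appears as |
|---|---|---|---|
| 0.10 | 0.5 | 0.05 | 0.45 |
| 0.10 | 1.0 | 0.10 | 0.40 |
| 0.20 | 0.5 | 0.10 | 0.40 |
| 0.20 | 1.0 | 0.20 | 0.30 |

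Among 20 evaluable controls, 10 to 20% is 20 × 0.10 = 2 to 20 × 0.20 = 4 people. At q = 0.30, outside the main range, the shift would be 0.15 to 0.30 SD.

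**Set against what the comparison can detect.** I took a two-sided alpha of 0.05 (assumed, as the article states none), 20 evaluable controls and 57 × 0.95 ≈ 54 evaluable fatigued patients. The smallest difference detectable with 80% power is then about 0.74 SD. With 20 v 20 it is about 0.91 SD. If a true 0.74 SD deficit shrinks by 0.05 to 0.20 SD, it appears as 0.69 to 0.54 SD, and power with 54 v 20 falls from 80% to about 74% to 53%.

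**The case against.** The strongest reply concerns scope. A reader might infer that Table 1 is applied only to the fatigued group. The article does not say so:

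- It calls the criteria those of the study, and the sentence that cites them describes how fatigued patients are recruited.
- Both groups come from one screened source: "Patients who have been curatively treated for cancer and finished treatment at least one year before, will be asked by their physician to fill out".
- In the abstract, both groups are named, and the text then says: "Participants should have completed treatment of a malignant, solid tumour minimal one year earlier and should have no evidence of disease recurrence".
- Both groups have MR measurements, so the MR contra-indication must in practice cover controls.
- The exclusion of antidepressants, anti-epileptics and benzodiazepines carries no restriction to cases.

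This part of the reply stands. The wider reading is an inference from silence, and I do not make it.

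The reply also notes that exclusion 1 has an ordinary purpose, which is to separate postcancer fatigue from fatigue with another somatic cause. A site might read it as naming a type of disease, one capable of causing fatigue, and apply it to everyone. Figure 1 and the full protocol are not shown and may describe how controls are screened. That is possible, and it is why the imbalance is a risk and not an established fact. The published criterion would still need wording that does not depend on fatigue.

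Finally, survivors who are not severely fatigued despite such disease may be fewer or less severely ill than survivors at large, so 10 to 20% may be too high. This is fair, and the figures are illustrative only.

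**Conclusion.** The point holds as one of wording and a resulting risk of bias. Read literally, exclusion 1 can remove only fatigued survivors whichever way the scope of Table 1 is read, and neither the stated matching nor the stated analysis corrects for it. The likely consequence is attenuation of true differences in the baseline comparison, by 0.05 to 0.20 SD under the assumed inputs.

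Three stronger conclusions are not supported:

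- *The groups do differ by selection.* The article shows only that they could.
- *The bias would reverse a true deficit.* Under the assumed range, that would need a true deficit smaller than 0.20 SD.
- *No other planned analysis bears on the question.* The article also plans to relate daily fatigue levels to the (neuro)physiological measures, and to analyse change over six months.

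The randomised comparison of CBT with waiting list is untouched, because both arms are drawn from the fatigued group. The change should still be made, since asymmetric selection cannot be undone by wording once controls are recruited.

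**What to change.** Make two small edits:

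1. Under Study population, state that Table 1 applies to both fatigued and non-fatigued participants.
2. Reword exclusion 1 so that it does not depend on the participant being fatigued. For example, it could exclude physical comorbidity known to cause fatigue or to impair the measured outcomes (exercise capacity, neuromuscular function, brain MR measures), judged by the same list in both groups.

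This is about one sentence in the text and one line in the table. The downside is that a few more potential controls will be screened out, so more may have to be approached to reach 21. The sample size and the randomised part of the trial do not change.

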**Figure 1 F1:**
[figure not shown]
Flow-chart of the study.

### Randomization and intervention

As shown in Figure 1, severely fatigued patients will be randomized to either the intervention group (75%) or the control group (25%). Randomization will take place per patient. Patients randomized to the intervention group will be treated with CBT for PCF, as described previously.[14] The treatment consists of 12–14 individual sessions in six months. Patients randomized to the control group will be treated with CBT after six months.

### Outcome measures

#### *Peripheral and central fatigue*

To obtain maximal voluntary contraction (MVC) of the biceps brachii muscle, participants will make MVCs, with 1 min intervals, until no further force increase was observed. After a rest period of 10 min, peripheral and central fatigue will be measured during a 2 min sustained MVC of the biceps brachii muscle.[18] During these 2 min, electrical endplate stimulation over the motor points of the medial and lateral head of the biceps brachii muscle will be applied every 15 s, leading to superimposed force responses. Patients will be verbally encouraged to perform maximally throughout the 2 min. An indicator of peripheral muscle fatigue is MFCV, which will be measured using sEMG.[16] Peripheral muscle fatigue will also be quantified by measuring the muscular force response to electrical endplate stimulation before and after the test. An indicator of central muscle fatigue is additional force production upon electrical endplate stimulation during exercise.[18] Submaximal central activation during exercise, or CAF, will be measured using a twitch interpolation technique.[19]

#### *Brain morphology and metabolism*

Global volumes of gray and white matter, subcortical brain volumes, and brain metabolite concentrations will be obtained. MR measurements will be performed on a 3 Tesla MR System using a radiofrequency head coil. High resolution (1 mm^3^), T1 weighted MR images of the whole brain will be acquired using a magnetization prepared rapid acquisition gradient echo (MPRAGE) sequence. Normalizing, bias-correcting, and segmenting into global volumes of gray and white matter will be performed using the VBM method.[41] Automatic segmentation of subcortical brain structures was performed using the FIRST module of FSL.[42]

^1^ H MR spectroscopic imaging (MRSI) will be performed, with special interest for the hippocampus, the occipital cortex, the frontal cortex, and the ventricles. The ^1^ H MRSI will allow the identification and quantification of metabolites like choline, creatine, N-acetylaspartate, and lactate. Volume selection will be performed with a semi-localized by adiabatic selective refocusing (semi-LASER) pulse sequence [43] with a repetition time of 1500 ms, an echo time of 30 or 136 ms, and a voxel size of 10 mm^3^. The data will be analyzed using LCModel software.

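### The baseline t test of brain volumes, fatigued v non-fatigued, has no head-size term; this costs precision and lets a head-size imbalance shift the estimate

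*Protocol article*

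**What the plan says.** The abstract of the Protocol article lists brain morphology among the primary outcomes: "Primary outcome measures are fatigue severity, central and peripheral fatigue, brain morphology and function, and physical condition and activity".

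The section Brain morphology and metabolism defines the measures: "Global volumes of gray and white matter, subcortical brain volumes, and brain metabolite concentrations will be obtained". It describes two processing routes:

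- Global volumes: "Normalizing, bias-correcting, and segmenting into global volumes of gray and white matter will be performed using the VBM method".
- Subcortical volumes: "Automatic segmentation of subcortical brain structures was performed using the FIRST module of FSL".

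Statistical analysis assigns independent samples t tests to the fatigued v non-fatigued comparison, for the purpose of "testing baseline differences in primary and secondary outcome measures between fatigued and non-fatigued cancer survivors". The only covariates in that section belong to the randomized comparison: "Baseline differences between the therapy and waiting list condition are entered as covariates in further analyses".

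Study population gives the matching factors: "Severely fatigued patients will be matched with non-fatigued patients with respect to age, sex, and previous cancer treatment". Neither head size nor intracranial volume is named anywhere in the article.

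**The concern.** Larger heads hold larger brains, so part of the spread in a brain volume between people reflects head size and says nothing about fatigue. A two-sample t test leaves that part in the error term. Sex matching deals with the head-size difference between men and women, but not with variation within a sex.

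The groups are also not randomized. The fatigued patients are those referred to a specialist fatigue centre, and the others are chosen to match them. Any head-size difference between the groups, by chance or through selection, enters the volume difference directly.

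The article hopes for an objective biological marker of fatigue. A volume difference that head size could explain would be weak evidence for one, and a real but moderate difference could be missed.

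**Working it through.** **The plan's own power figure.** The only power statement concerns CIS-fatigue: at least 80% with 30 v 10 patients and success rates of 67% v 10%. At a two-sided 5% level (assumed, since none is stated), the normal approximation gives 95% and exact enumeration of Fisher's test gives 89%, so the statement holds. It does not bear on brain volumes. For those, Power calculation offers only precedent from other studies, with no effect size, SD or power.

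**Inputs.**
- Planned numbers: 57 fatigued and 21 non-fatigued (Study population).
- Technically insufficient measurements: 5% (Power calculation). The 20% drop-out does not apply at baseline.
- Evaluable: 57 × 0.95 = 54.15 and 21 × 0.95 = 19.95, so about 54 v 20.
- Correlation r of a volume with intracranial volume within groups: not in the article. Assumed range 0.3 to 0.9; it may differ between global and subcortical volumes.

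**Unadjusted test.** The standard error of the difference, in SD units, is √(1/54 + 1/20) = 0.262. With 72 degrees of freedom, a two-sided 5% t test has 80% power for 0.74 SD. For a true difference of 0.5 SD the noncentrality is 0.5/0.262 = 1.91 and the power is 47%.

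**Adjusted test.** A head-size covariate multiplies the residual SD by √(1 − r²) and uses one more degree of freedom (71 left). The noncentrality becomes 0.5/(0.262 × √(1 − r²)).

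| r | share of variance, r² | √(1 − r²) | detectable at 80% power (SD) | power at 0.5 SD |
|---|---|---|---|---|
| none (t test) | – | 1 | 0.74 | 47.0% |
| 0.3 | 9% | 0.954 | 0.71 | 50.6% |
| 0.5 | 25% | 0.866 | 0.64 | 58.5% |
| 0.7 | 49% | 0.714 | 0.53 | 75.1% |
| 0.8 | 64% | 0.600 | 0.45 | 88.1% |
| 0.9 | 81% | 0.436 | 0.32 | 99.1% |

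The table ignores the small price of estimating the slope when the groups differ slightly in head size by chance. On average that raises the variance by a factor of about 1 + 1/(74 − 4) = 1.014. The adjusted powers then become 50.1%, 57.9%, 74.5%, 87.7% and 99.0%, so the picture does not change.

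**Effect of an imbalance.** The chance difference in mean head size also has a standard error of 0.26 SD. An imbalance of one standard error moves the unadjusted volume difference by r × 0.26 SD: 0.13 SD at r = 0.5 and 0.21 SD at r = 0.8.

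Given an imbalance of k standard errors, the false-positive risk of the unadjusted test (normal approximation) is 1 − Φ((1.96 − rk)/√(1 − r²)) + Φ((−1.96 − rk)/√(1 − r²)). At k = 2 this is 13%, 22%, 27% and 36% for r = 0.5, 0.7, 0.8 and 0.9. At k = 1 it is below 5% (4.8%, 3.9%, 2.7% and 0.8%). Averaged over all chance imbalances it is 5%.

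**The case against.** The strongest reply is that scaling for head size is a detail of the imaging pipeline. The article is condensed, cites method papers for both segmentations, and gives one generic sentence on t tests for all outcomes. A t test on volumes already scaled to head size would fit that sentence. This stands as a reason for caution: the full protocol may contain a correction. But the article does fix a test without covariates for a primary outcome, and it mentions covariates where it intends them, in the randomized comparison.

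Three stronger readings are tempting, and the article does not support them.

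- **The volumes are certainly absolute.** The article never says so. Normalizing is listed for the global volumes without explanation, so it cannot be read as a head-size correction or ruled out as one. For the subcortical volumes no such step is named.
- **Most of the error is head-size noise.** That needs r² above 0.5, so r above about 0.71. The article gives no correlation or variance share, and at r = 0.5 the share is only 25%.
- **The t test is invalid.** Its standard error already includes head-size variation, so it holds 5% on average over chance imbalances. Matching on sex also limits the imbalance tied to sex.

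Two further points are fair. The 0.74 SD figure reflects the group sizes and applies to any outcome compared at baseline. The article also names segmentation into gray and white matter only, so a cerebrospinal fluid (CSF) volume may have to be added to obtain intracranial volume.

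**Conclusion.** The point holds as one of precision and of protection against imbalance, for the baseline comparison only. As written, the plan compares a primary outcome made of brain volumes with no head-size term, and neither matching nor the stated processing clearly supplies one.

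The gain from adjustment is positive at every r considered, but its size is not known from the article. It is small at r = 0.3 (about 4 percentage points of power at 0.5 SD) and large at r = 0.8 (about 41 points). These figures assume 54 v 20 evaluable participants, a two-sided 5% level, and a linear relation with the same slope in both groups. The overall type I error under chance imbalance is not at issue. A systematic head-size difference between the groups would, however, bias the unadjusted estimate.

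**What to change.** For baseline comparisons of global gray matter, white matter and subcortical volumes between fatigued and non-fatigued participants, replace the t test with a linear model (ANCOVA) containing group and total intracranial volume. Specify this before the data are examined.

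- **Covariate.** Derive it from the same T1 images as gray + white + CSF, adding the CSF class to the segmentation output if it is not already kept. CSF belongs in the sum: without it, a true loss of gray matter would lower the covariate too, and the adjustment would remove part of the effect sought.
- **Volumes.** Use native-space volumes for both segmentation routes, and state what the normalizing step does, so that head size is not corrected twice.
- **Follow-up.** The 6-month change needs no head-size term. Head size is constant within a patient, so it largely drops out of the within-patient change.

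The cost is one degree of freedom and a small amount of processing. No extra scan or participant is needed.
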